### **9.2.3 Suspected unexpected serious adverse reactions (SUSARs)**

Not applicable

## **9.3 Annual safety report**

Not applicable

#### 9.4 Follow-up of adverse events

All AEs that have occurred within the first four post-operative weeks will be followed until they have abated, or until a stable situation has been reached. Depending on the event, follow up may require additional tests or medical procedures as indicated, and/or referral to the general physician or a medical specialist.

SAEs need to be reported till end of study within the Netherlands, as defined in the protocol

#### 9.5 Safety Committee

Both treatment strategies (laparoscopic (intervention) and open (control) hernia repair) are currently performed in children with inguinal hernia who need to undergo repair. Consequently, there are no additional risks for subjects of this study and it is therefore not necessary to install a DSMB. Because this study is undertaken in children, the investigators do want to install a safety committee, which can be asked for help if a SAE is encountered.

The committee will be formed by a paediatric surgeon ([REDACTED]), [REDACTED], [REDACTED], [REDACTED], a surgeon with expertise in hernia repair ([REDACTED]), [REDACTED], and a paediatrician ([REDACTED]).

## 10. STATISTICAL ANALYSIS

### 10.1 Primary study parameter(s)

We will create a 2x2 contingency table with the children that underwent open or laparoscopic repair or not versus the children with and without a ipsilateral recurrent or MCIH hernia in the year after surgery. A chi-square test will be performed and the relative risk, absolute risk difference and odds ratio with their 95% confidence intervals will be calculated. In addition, effect modification will be assessed for gestational age, age at the time of surgery, sex and initial hernia side to identify whether the effect of a treatment is different in groups of patients with different characteristics. Mean differences and corresponding 95% confidence intervals will be calculated for duration of operations (including anaesthesia). Risk differences and 95% confidence intervals will be calculated for complications. Logistic regression analysis will be performed to adjust for possible confounders (i.e. prematurity, side of inguinal hernia), if necessary. All analyses will be performed according to the intention-to-treat principle. Missing values will be analysed using multiple imputation.

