### **4.4 Sample size calculation**

Reoperation includes both MCIH and recurrence rates. Since recent studies showed that the recurrence rate is similar between the open and laparoscopic group (0.3 vs 0.2% (12)), we used reoperation rates due to MCIH to calculate our sample size. The latest IPEG guidelines states that the MCIH rate after open repair is 6-8%. We expect that the laparoscopic repair reduces the MCIH rate to 1% since the CPPV will be closed during the same procedure. Thus, re-operation based on MCIH is performed in approximately 6% patients in the open group and in approximately 1% in the laparoscopic PIRS group. We consider a reduction of 5% of children requiring reoperation clinically relevant.

A total sample size of 422 patients is needed to detect such a reduction with a power of 0.80 at a two-sided alpha of 0.05 (nQuery Advisor 7.0). Taking into account 10% loss to follow-up we need to include 464 children. Since approximately 800-850 paediatric patients a year undergo inguinal hernia repair in our participating centres, we expect to reach our sample size within one to two years after the start of the trial. After one year of follow-up, we will perform an interim analysis to assess the effect of both treatment strategies.

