## **8.2 Randomisation, blinding and treatment allocation**

When parents/caretakers provide informed consent, the child will be randomly assigned (1:1) to the intervention (laparoscopic repair) or control group (open repair) using a web-based application with a computer-generated list with random block sizes of four or six and rendered by an independent data manager. The block size of the randomisation scheme is unknown to the study personnel. Participants and investigators are aware of allocation; masking is impossible because of the nature of the intervention.

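### With about 2 PIRS events expected, ratio-scale treatment interactions for sex and hernia side each have roughly a 45–75% chance of having no finite estimate

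*Protocol*

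**What the plan says.** Protocol Section 4.4 bases the sample size on reoperation for a metachronous contralateral hernia: "re-operation based on MCIH is performed in approximately 6% patients in the open group and in approximately 1% in the laparoscopic PIRS group". It continues: "A total sample size of 422 patients is needed to detect such a reduction with a power of 0.80 at a two-sided alpha of 0.05". With 10% loss to follow-up the inclusion target is 464, randomised 1:1 (Section 8.2). Section 4.4 also gives recurrence rates of 0.3% (open) and 0.2% (laparoscopic). Recurrence counts towards the primary endpoint in Section 8.1.1 but was left out of the sizing.

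Section 10.1 compares the arms with a chi-square test and says "the relative risk, absolute risk difference and odds ratio with their 95% confidence intervals will be calculated". It then states that "effect modification will be assessed for gestational age, age at the time of surgery, sex and initial hernia side", in order to see whether the treatment effect differs between groups of patients. Logistic regression adjusting for prematurity and side is planned on condition that it proves necessary. The section does not state the scale or model for effect modification, does not say whether the two age variables are grouped or continuous, and names no method for sparse data.

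**The concern.** The trial is sized to detect one overall difference that is expected to rest on very few events in the PIRS arm. Splitting those events by sex, side or an age group will often leave a subgroup with none. The interaction odds ratio or ratio of relative risks is then zero or infinite. Ordinary software may still print a very large estimate with an unusable interval, and that output can be misread as evidence that the effect differs between subgroups. To a lesser degree, the overall odds ratio and the adjusted logistic model have the same weakness.

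**Working it through.** **Inputs.** 6% and 1%, total 422, power 0.80, two-sided alpha 0.05, inclusion of 464, and recurrence of 0.3% and 0.2% (all Section 4.4); 1:1 allocation (Section 8.2). Subgroup shares are not in the protocol, so splits from 50:50 to 10:90 are assumed, equal in both arms and with no true effect modification.

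**The protocol's own figure.** Pooled-variance formula without continuity correction, mean rate 0.035:

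n per arm = [1.96·√(2·0.035·0.965) + 0.842·√(0.06·0.94 + 0.01·0.99)]² / 0.05² ≈ 210.9, so 211 per arm and 422 in total. This matches. Also 422 × 1.10 = 464.2, the stated 464, or 232 per arm.

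**Expected events at 211 per arm.** Open 211 × 0.06 = 12.7; PIRS 211 × 0.01 = 2.1; total 14.8. With recurrence added (6.3% and 1.2%): 13.3 and 2.5.

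**Overall odds ratio.** It is not finite when the PIRS arm has no events:
- 211 per arm, 1%: 0.99^211 = 12.0%
- 232 per arm, 1%: 0.99^232 = 9.7%
- 211 per arm, 1.2%: 0.988^211 = 7.8%
- 232 per arm, 1.2%: 0.988^232 = 6.1%

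**Adjusted logistic model (arm, prematurity, side).** In 1,500 simulated trials of 211 per arm, with an assumed 20% premature and 40% on one side, separation occurred in about 16%. There are 14.8 / 3 ≈ 5 events per parameter.

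**Interaction with a binary modifier.** The estimate is not finite if any of the four arm-by-level cells has no event. Worked example, 211 per arm split 40:60 (84 and 127 children):

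1 − (1 − 0.99^84)(1 − 0.99^127)(1 − 0.94^84)(1 − 0.94^127) = 1 − 0.570 × 0.721 × 0.9945 × 0.9996 = 59%.

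| Split | 211 per arm, 6% v 1% | 211, recurrence added | 232, 6% v 1% | 232, recurrence added |
|---|---|---|---|---|
| 50:50 | 57% | 48% | 53% | 43% |
| 40:60 | 59% | 50% | 54% | 45% |
| 20:80 | 74% | 68% | 71% | 64% |
| 10:90 | 88% | 85% | 86% | 83% |

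**Interaction with a modifier kept continuous.** In simulation this failed in about 11–12% of trials, nearly always because the PIRS arm had no events.

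**Precision when the estimate is finite.** Take 2 of 211 PIRS and 13 of 211 open events. The standard error of the log odds ratio is √(1/2 + 1/209 + 1/13 + 1/198) = 0.77, so the 95% interval runs a factor of exp(1.96 × 0.766) ≈ 4.5 either side of the estimate. Now split evenly, with one PIRS event in each half and 6 and 7 open events. The interaction has standard error √(1 + 1 + 1/6 + 1/7 + 0.04) = 1.53, and its interval runs about 20-fold in either direction. An interaction that is estimable therefore says very little.

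**The case against.** The strongest case against has four parts.

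- **The primary analysis is sound.** Under the null about 7.4 events are expected per arm (14.8 / 2), so the chi-square test is usable, and Section 10.1 already asks for the absolute risk difference with an interval. This stands.
- **The protocol does not commit to ratio-scale interactions or to cutting the age variables.** Subgroup risk differences would also fit the wording and can be calculated with an empty cell. This stands as a limit on the point: the figures apply to ratio-scale interactions with two-level modifiers. Still, odds ratios and logistic regression are the tools the section names, and its aim is phrased in terms of patient groups.
- **211 per arm without recurrence is the less favourable base case.** Correct. The table shows the alternatives, and the most favourable of them still gives 43%.
- **Interval method, penalisation and coding may sit in a statistical analysis plan that is not shown.** True of those details. However, the protocol itself commits to four effect-modification analyses on about 15 events, and no later choice of method supplies the missing events.

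A reader might go further in three ways that the document does not support. One is that the overall and adjusted odds ratios will usually fail; they are finite in about 88–94% and 84% of trials. Another is that failure of at least one of the four interactions is close to certain; that needs all four to be dichotomised, at shares the protocol does not give. The third is that the interim decision in Section 10.4 will use these analyses. That section foresees looking at whether to continue in a subgroup but does not refer to the Section 10.1 assessment.

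**Conclusion.** The point holds in limited form. On the protocol's own rates, the planned effect-modification assessment is badly matched to the data for sex and hernia side, and for age or gestational age if dichotomised. On a ratio scale each has roughly a 45–75% chance of no finite estimate (43–74% across splits from 50:50 to 20:80, higher for more uneven splits). The overall odds ratio (about 6–12%) and the adjusted model (about 16%) fail much less often but remain imprecise. The chi-square test and the risk difference are not affected. The result rests on the planning rates being right and on the assumed subgroup shares; a higher PIRS event rate would ease the problem.

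**What to change.** In Section 10.1:

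1. Give the already planned absolute risk difference a score-type interval (Miettinen-Nurminen or Newcombe), which remains valid with zero events in an arm. Because missing values are to be multiply imputed, state how the interval is combined across imputations.
2. For any adjusted odds ratio, use Firth penalised logistic regression with prematurity and side fixed in advance, in place of an adjustment made only where judged necessary.
3. Report effect modification as exploratory subgroup risk differences with intervals, and state that no decision rests on them.

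The cost is a few lines of wording and standard software options. The downside is weaker subgroup claims, which the expected number of events could not support anyway.

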### 10.2 Secondary study parameter(s)

Mean differences and corresponding 95% confidence intervals will be calculated for postoperative pain, duration of hospital admission, time to full recovery and cosmetic appearance. Logistic regression analysis will be performed to adjust for possible confounders (i.e. prematurity, side of inguinal hernia), if necessary. Peri- and post-operative complications will be analysed in a 2x2 contingency table and the data will be assessed by a Chi-Square test. The CPPV rate will only be analysed for the laparoscopic group, since the open repair does not allow for contra-lateral exploration.

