### **4.2 Inclusion criteria**

In order to be eligible to participate in this study, a subject must meet all of the following criteria: infants aged 0 months to 16 years of age with a primary unilateral inguinal hernia, undergoing hernia repair.

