## **12. ADMINISTRATIVE ASPECTS, MONITORING AND PUBLICATION**

### **12.1 Handling and storage of data and documents**

To ensure their privacy, all the participants' data will be encoded using a five-digit number that is only used for this study (XX-XXX). This encoding will be as follows: the first two digits are for the participating centre; the second three digits are for the consecutive patient number in that centre. Only the principal investigator, the coordinating investigator and the project leader will have access to the encoding key which links the code to the participants' personal data. After termination of the study, participants will have full access to their results and data will be explained to them when requested from the researcher at their site. This researcher can obtain the results via the coordinating investigator or the project leader. In case this study (by coincidence) reveals any findings important to participants, the principal investigator makes sure the attending doctor will be informed.

The start date of this study will be reported to the METc. All collected data will be stored at Amsterdam University Medical Center, location AMC, for a maximum of 15 years.

We will collect following baseline characteristics and data from the participants: inguinal hernia in first degree siblings, gestational age, birth weight, age at day of surgery, weight at day of surgery, duration of surgery, duration of hospital stay, sex, side of the hernia, comorbidity, CPPV rate, complications (wound infection, testicular atrophy, apnoea, recurrence), development of contralateral hernia.

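### The continuous secondary outcomes have no usable covariate adjustment: the only model named is logistic and omits age and sex, so some precision is probably lost

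*Protocol*

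**What the plan says.** Two sections of the protocol fix how the continuous outcomes are compared.

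- Section 10.2: "Mean differences and corresponding 95% confidence intervals will be calculated for postoperative pain, duration of hospital admission, time to full recovery and cosmetic appearance".
- Section 10.1, on operating time: "Mean differences and corresponding 95% confidence intervals will be calculated for duration of operations (including anaesthesia", with the parenthesis closing there.

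No covariates are attached to either sentence. Both sections then carry the same sentence on adjustment: "Logistic regression analysis will be performed to adjust for possible confounders (i.e. prematurity, side of inguinal hernia), if necessary". No other adjusted model is named for these outcomes, and no criterion says when adjustment becomes necessary.

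Age and sex enter the analysis only in section 10.1, for the primary parameter: "effect modification will be assessed for gestational age, age at the time of surgery, sex and initial hernia side". Both are among the data to be collected under section 12.1: "gestational age, birth weight, age at day of surgery, weight at day of surgery" and, further along the same list, "duration of hospital stay, sex, side of the hernia, comorbidity". The eligible population in section 4.2 is "infants aged 0 months to 16 years of age with a primary unilateral inguinal hernia". Section 8.2 describes 1:1 allocation in random blocks of four or six and mentions no stratification by age or sex.

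**The concern.** There are two linked problems. First, the model does not fit the estimand. Logistic regression models the odds of a binary outcome. It can serve complications or reoperation, but it gives no adjusted difference in minutes, days or pain points. As written, an analyst who judged adjustment necessary for operating time or hospital stay would have no usable method.

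Second, the covariates named are prematurity and hernia side. In a trial that takes both newborns and adolescents, age at surgery is an obvious candidate for explaining variation in these outcomes, and allocation does not balance it by design. Variation due to age or sex then stays in the residual error and widens the intervals. Section 8.3 expects the laparoscopic operation to be shorter and makes this a secondary objective, so precision on operating time has some value.

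**Working it through.** **The plan's own figure.** The only sample size stated is for the primary endpoint (section 4.4): 6% against 1%, two-sided alpha 0.05, power 0.80. With pooled variance and a mean proportion of 0.035:

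n per arm = [1.96 × sqrt(2 × 0.035 × 0.965) + 0.8416 × sqrt(0.06 × 0.94 + 0.01 × 0.99)]² / 0.05² = (0.5094 + 0.2167)² / 0.0025 = 210.9, so 211 per arm and 422 in total.

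This matches the protocol, and 422 × 1.10 = 464 matches the number to be included. Neither figure depends on this point. The protocol states no SD, target difference or precision for the continuous outcomes.

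**Inputs for the check.** 211 evaluable children per arm, N = 422 (section 4.4). R2, the share of outcome variance explained by age and sex, is not in the document and is therefore varied.

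**Unadjusted precision.** 95% half-width = 1.96 × SD × sqrt(2/211) = 0.191 SD.

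**Adjusted precision.** A linear model with arm and two covariate terms multiplies the half-width by sqrt[(1 − R2) × (N − 2)/(N − 4)] = sqrt[(1 − R2) × 420/418]. The large-sample factor is sqrt(1 − R2). The equivalent sample size is N/(1 − R2).

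| Assumed R2 | Adjusted half-width (SD) | Narrower by, large sample | Narrower by, degrees of freedom counted | 422 children behave like |
|---|---|---|---|---|
| 0 | 0.191 | 0% | 0.2% wider | 422 |
| 0.02 | 0.189 | 1.0% | 0.8% | 431 |
| 0.05 | 0.186 | 2.5% | 2.3% | 444 |
| 0.10 | 0.182 | 5.1% | 4.9% | 469 |
| 0.20 | 0.171 | 10.6% | 10.3% | 528 |
| 0.30 | 0.160 | 16.3% | 16.1% | 603 |

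**Break-even.** (1 − R2) × 420/418 = 1 gives R2 = 2/420, about 0.5%. With a flexible age term, say three terms plus sex, the worst case at R2 = 0 is sqrt(420/416) = 1.005, or 0.5% wider, and break-even is 4/420, about 1%.

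**Validity of the unadjusted intervals.** In 2,000 simulated trials of 422 children at each of R2 = 0, 0.10 and 0.30 (age uniform over 0 to 16 years, sexes equal, outcome linear in age), the ratio of adjusted to unadjusted standard error averaged 1.00, 0.95 and 0.84. Coverage of the nominal 95% intervals lay between 94.65% and 96.0% for both analyses. The loss is one of precision, not of validity.

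**Why the primary analysis is left alone.** Expected events are 211 × 0.06 + 211 × 0.01 = 12.7 + 2.1, about 15. That is too few to carry additional covariates.

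**The case against.** The strongest reply is that covariates for secondary outcomes are commonly left to the statistical analysis plan, which is not shown, and that the list in brackets may be illustrative. This stands in part: nothing bars a later plan from adding age and sex. But the protocol is not silent. It names a model for outcomes that it reports as mean differences, and that model cannot deliver them.

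Three stronger readings are tempting, and the document does not support them.

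- A reader might infer that the planned comparisons are biased, or that a chance age imbalance invalidates them. They are not biased. Under 1:1 randomisation the unadjusted difference is unbiased, and its interval already allows for chance imbalance.
- A reader might infer that age and sex are the strongest recorded predictors, so that a large gain is assured. The protocol gives no SD, no R2 and no association with these outcomes. It also records gestational age, birth weight, weight and comorbidity. For sex, the support is limited to operative steps that section 5.2 describes only in boys, which makes a link with operating time plausible but says nothing about stay, pain or recovery. Listing age and sex as possible effect modifiers of the primary outcome is a different question from whether they predict the secondary ones.
- A reader might quote only the upper end of the R2 range. The gain may be negligible for some outcomes, and the low end belongs in the range.

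It is also fair to object that one linear model does not suit every outcome. Pain is measured on two instruments (CHIPPS and VAS, section 8.1.2), and hospital stay is counted over a year and is likely to be skewed. Both points stand and shape the fix.

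**Conclusion.** The point holds as a low-severity gain in precision on secondary outcomes. The mismatch between a logistic model and a mean difference is plain from the text. The size of the loss is not: it rests wholly on an assumed R2, from no gain at zero to intervals about 16% narrower at 0.30, against a worst-case cost of a fraction of a percent. It also assumes that the linear model describes the age relation reasonably and that about 422 children contribute data to each outcome. The unadjusted intervals remain valid, and the primary endpoint, the 422 and the 464 are unaffected.

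**What to change.** In sections 10.1 and 10.2, keep the logistic sentence for binary outcomes only. For duration of operations, pain, hospital stay and time to recovery, replace it with a linear model containing arm, age at surgery as a flexible term (a spline, for example) and sex, specified in advance and fitted regardless of observed imbalance. Report the adjusted mean difference with its 95% interval, and keep the unadjusted difference as support. Fit pain separately for CHIPPS and for VAS. Use robust or bootstrap intervals for skewed outcomes such as hospital stay. Leave the primary 2x2 comparison unchanged. Cosmetic appearance, a five-point score, is outside this change.

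The cost is a change of wording, a few degrees of freedom and slightly more analysis work. No new data are needed.

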#### Definitions

*Testicular atrophy*: Complete testicular atrophy: no palpable testicular tissue in scrotum.

*Partial testicular atrophy*: Testis documented to be smaller at follow-up than at time of inguinal hernia repair.

*Wound infection/Surgical site infections*: Infection, occurring within 30 days of surgery, involving only the skin and subcutaneous tissue. Purulent discharge or organisms isolated from aseptically obtained wound culture must be present. Also at least one of the following signs of infection must be present: Pain or tenderness, localized swelling and redness or heat.

*Apnoea*: An unexplained episode of cessation of breathing for 20 seconds or longer, or a shorter respiratory pause associated with bradycardia, cyanosis, pallor, and/or marked hypotonia.

Total duration of surgery (including anaesthesia) related to primary open or laparoscopic inguinal hernia repair.

Postoperative pain measured according to the children and infants post-operative pain score (CHIPPS) and VAS and pain medication requirement related to post-operative pain within 2 weeks after primary operation.

Length of hospital stay related to inguinal hernia within one year after primary operation.

Time to full recovery within one year after primary operation.

CPPV rate during laparoscopic contra-lateral exploration in the PIRS group. When seen, the CPPV will be corrected.

MCIH rate within one year after primary operation.

Cosmetic appearance scored on a 5-Likert scale from 1-5 (1= bad, 2=unsatisfactory, 3=satisfactory, 4=good, 5=excellent) within one year after primary operation. Cosmetic appearance will be scored 4 weeks and 1 year after primary surgery.

Cost-effectiveness will be assessed from a societal and health care perspective and will include cost of surgery, hospitalization, control visits, re-operation, complications and loss of productivity of the parents/caretakers. Most data will be registered in the medical records; specific data entry forms will be used. Data on productivity loss will be collected by online questionnaires before surgery, four weeks after surgery, one year after surgery and in case of a recurrence or MCIH, four weeks after re-operation. Cost of the operation will be measured using a bottom-up micro costing approach. Other costs will be valued using guideline prices.

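### Section 10.2 names logistic regression as the only adjustment model for four non-binary outcomes compared by mean difference, and has no method for recovery times that are only partly observed

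*Protocol*

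**What the plan says.** Section 10.2 opens with the effect measure for four outcomes: "Mean differences and corresponding 95% confidence intervals will be calculated for postoperative pain, duration of hospital admission, time to full recovery and cosmetic appearance". The end of that list runs straight into the adjustment model: "time to full recovery and cosmetic appearance. Logistic regression analysis will be performed to adjust for possible confounders (i.e. prematurity, side of inguinal hernia". The adjustment is to be made only if needed. The binary outcomes of that section come only afterwards: "Peri- and post-operative complications will be analysed in a 2x2 contingency table and the data will be assessed by a Chi-Square test".

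Section 8.1.2, under its definitions, sets the scales. Pain is "Postoperative pain measured according to the children and infants post-operative pain score (CHIPPS) and VAS". Stay is "Length of hospital stay related to inguinal hernia within one year after primary operation". Recovery is "Time to full recovery within one year after primary operation". Cosmetic appearance is a five-point Likert score taken at four weeks and at one year.

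Section 10.1 treats duration in the same way, "Mean differences and corresponding 95% confidence intervals will be calculated for duration of operations (including anaesthesia", then gives risk differences for complications, and then repeats the logistic sentence. It also states that all analyses follow intention-to-treat and that missing values are handled by multiple imputation.

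**The concern.** Logistic regression models a yes/no outcome and returns an odds ratio. Read in order, section 10.2 asks it to adjust differences in means of scores and durations. An analyst who follows the text must either abandon the stated model or split each outcome at a cut-point that the protocol does not give. A split also replaces the declared effect measure with another one. Adjustment is made only if judged necessary, with no criterion, and section 8.2 says that allocation is known to investigators. The choice of whether and how to adjust could then be made with the results in view.

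Time to full recovery is a time to an event inside a one-year window. Children who leave early, or who have not recovered at one year, have no completed time, and a plain mean difference gives no rule for them.

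**Working it through.** **1. The plan's own figure.** Section 4.4 states 422 children for 6% versus 1%, power 0.80, two-sided alpha 0.05. With the pooled-variance formula and 1:1 allocation (section 8.2):

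n per arm = [1.960 × √(2 × 0.035 × 0.965) + 0.842 × √(0.06 × 0.94 + 0.01 × 0.99)]² / 0.05² = (0.509 + 0.217)² / 0.0025 ≈ 211, so 422 in total, with power 0.800.

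The figure reproduces. It rests on the binary primary endpoint, so nothing below touches it.

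**2. Outcome, declared measure and named model.**

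| Outcome in 10.2 | Scale in 8.1.2 | Declared measure | Model named next |
|---|---|---|---|
| Pain | CHIPPS and VAS scores | mean difference | logistic |
| Hospital stay | duration | mean difference | logistic |
| Time to full recovery | time within one year | mean difference | logistic |
| Cosmetic appearance | score 1 to 5 | mean difference | logistic |

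The model is log[p/(1 − p)] = a + b × arm + c × covariates, where p is the probability of a yes. Its treatment effect is the odds ratio exp(b). No term in it is a difference in means. As a check, a binary logit was fitted to a score running from 1 to 5, and the software refused because the outcome must lie between 0 and 1. The protocol gives no cut-point for any of the four outcomes and names no linear, ordinal or time-to-event regression anywhere.

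**3. Which outcomes the logistic model does fit.** Reoperation (8.1.1), complications and the contralateral hernia rate (8.1.2) are all binary. In 10.1 the logistic sentence follows the risk differences for complications and sits in the section on the binary primary endpoint, where it is suitable.

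**4. What is observed of recovery time.** Section 8.3 schedules a call at four weeks that asks about recovery. The next planned contacts are the questionnaire and call at one year. Section 8.4 allows withdrawal at any time, and section 4.4 allows for 10% loss to follow-up. Three kinds of incomplete time can arise:

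- A child not recovered at four weeks and then lost: the time is known only to exceed about 28 days.
- A child not recovered at one year: the time exceeds the window.
- A child not recovered at four weeks but recovered by the one-year call, with no date recorded: the time lies between the two contacts.

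Ordinary multiple imputation treats each as a blank. It can fill in a value below 28 days for the first child, although the data exclude it. A censored or interval-censored analysis uses the bound.

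**The case against.** The strongest defence is that the logistic sentence in 10.2 repeats the one in 10.1 and was meant for binary outcomes. The link to the mean differences comes from sentence order, not from an explicit statement. This is plausible. But the sentence stands directly after the four non-binary outcomes and before the binary ones, and it is the only adjustment model in the section. On the generous reading its scope is still unclear and should be stated.

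A second defence is that the declared estimates are unadjusted mean differences, which randomisation makes valid without adjustment. That stands, and it limits the point to the adjusted secondary analyses.

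A reader might go further in three ways that the documents do not support.

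- *That duration of surgery in 10.1 has the same defect.* A sentence on risk differences for complications stands between it and the logistic sentence, which fits the primary endpoint there. Naming a model for duration is a matter of clarity.
- *That the plan throws away about a third of the information.* This follows from splitting a normal outcome at its median, and the protocol proposes no such split.
- *That mean recovery time is biased downward and favours the arm with more unrecovered children.* This needs those children to be dropped. Section 10.1 states intention-to-treat and multiple imputation, so a complete-case mean is not what is planned.

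**Conclusion.** The point holds as a mismatch between outcome and model in section 10.2. Followed as written, the named model cannot give an adjusted mean difference for pain, hospital stay, recovery time or cosmetic score without cut-points that the protocol does not state. The recovery endpoint also needs a method that uses partial information on children not known to have recovered.

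The reach is limited to adjusted secondary analyses and the recovery endpoint. The primary analysis and the sample size stand. No size or direction of bias can be given: the documents do not say how many children will be unrecovered at either contact, and if nearly all recover within weeks the recovery point will matter little. The 10% loss in section 4.4 is a planning allowance, not an estimate for this endpoint. The conclusion assumes that section 10.2 is read in the order in which it is written.

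**What to change.** In section 10.2:

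- Restrict logistic regression to the binary outcomes: reoperation, complications and contralateral hernia.
- State linear regression with robust or bootstrap intervals for adjusted mean differences in pain, hospital stay and cosmetic score. For clarity, say the same for duration of surgery in 10.1. Linear regression keeps the declared measure for the cosmetic score; an ordinal model would be a preference, not a correction.
- Fix the covariates in advance (gestational age or prematurity, and hernia side) in place of the open condition on need.
- For time to full recovery, name a time-to-event summary, for example restricted mean time to one year. Children not known to have recovered are censored at the last contact at which they were known to be unrecovered, or treated as interval-censored if no recovery date is recorded.

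The regression changes cost wording only, since section 12.1 already lists gestational age and side among the data collected. For recovery, the protocol does not say whether a date is recorded. If it is, the change is again wording. If not, the choice is an interval-censored analysis or one added item on the data form.
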